### Randomisation

Participants will be allocated to closed groups in which they will undergo the programme. Allocation occurs through an algorithm which assigns participants to groups based on age and sex. Groups consist of male only, female only, and mixed sex groups plus mostly older, mostly younger, and mixed age groups. Only groups that have between 28 and 32 participants will be included in the trial, to ensure a similar number of participants will be included in each experimental condition. Groups in which the number of participants falls outside this range will continue to the standard Second Nature programme. Each eligible group will be cluster randomised to one of 16 experimental conditions. The research team will use computerised randomisation software (MinimPy version 2) to randomly allocate the groups with a minimisation algorithm to balance sex and age across the experimental conditions as much as possible. Randomisation will be performed by a researcher who will not be delivering the intervention and who does not have visibility of the screening process or the allocation of groups.

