### Blinding

All participants will be blind to treatment allocation. Due to the nature of the interventions, the health coaches who will be delivering the intervention cannot be blinded, but they will not be involved in data analysis.

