**Fig. 3 Fig3:**
[figure not shown]
Example Second Nature core programme content

At the start of the programme, each participant receives a hard-copy instructional handbook and recipe book. Second Nature provides a 12-month programme consisting of three 4-month phases: (1) ‘Core’ (weeks 1–17), where participants receive support from their peers and health coach, and acquire knowledge of nutrition and habit formation; (2) ‘Growth’ (weeks 18–34), where participants gain a deeper understanding of their new behaviours and reinforce their new habits; and (3) ‘Maintain’ (weeks 35–52) where participants practice the skills they have learned to maintain their weight loss and continue to lose weight. The ‘core’ 17-week programme consists of mentoring from a health coach, who is either a registered dietitian or nutritionist, who delivers personalised support via a text-based messaging service within the app. The messaging support will be provided both privately and within a group chat of around 30 other participants. The minimum standard frequency for group messages is as follows: weeks 1–4: four messages per week; weeks 5–8: three messages per week; weeks 9–15: two messages per week; weeks 16–17: three messages per week. The group chat is monitored by the health coach, any comments or questions are answered, and further conversation is facilitated where possible. The private chat is only visible to the health coach and the participant and allows participants to ask specific questions on topics such as health-related issues and personalised dietary requirements. All participants within each experimental condition will be in the same group chat and will be assigned to the same health coach. Educational information, delivered by plain text, audio, and videos can be accessed by participants through the app (Table 3). Participants can record and view their weight and step count within the tracking section of the app, which can also be viewed by the participant’s health coach. Participants who have low engagement (defined as < 10 interactions with the app in the previous week) receive automated messages to encourage participation. Whilst weight monitoring is typically self-directed in the standard Second Nature programme, participants in this trial will be prompted by their health coach to weigh themselves at four specific timepoints within the programme (baseline, week 4, week 16, and week 24) to increase follow-up.

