**Table 3 Tab3:** Educational content during each week of the second nature programme

**Week**	**Topic**	**Description**
1	Kickstart week	Introduction to the programme and healthy habits
2	The psychology of eating	The ‘why’ behind certain food choices and overcoming the common obstacles to weight loss
3	Unpacking nutrition	Introduction to nutrition recommendations and common dieting myths
4	The relationship between weight and health	Set point theory, weight loss plateaus, and ways of measuring progress
5	Breaking and making habits	Habit formation, the value of ‘tiny habits’, and stopping unhelpful habits
6	Appetite and cravings	Managing cravings and understanding factors that influence appetite
7	Mindset	Thinking traps, strategies to overcome common thought patterns, and an introduction to body image
8	Stress and emotions	How stress and emotions affect food choices; introduction to mindfulness and emotional eating
9	Exercise	Common barriers to exercise and strategies to incorporate more exercise into daily life
10	Hunger and fullness	The biology and psychology of hunger and fullness and how to be more mindful of fullness cues
11	Nutrition myths	Counting macros, protein intake, alcohol, sweeteners, and reducing risk of heart disease
12	Sleep	The impact of sleep on weight loss and strategies to improve sleep quality
13	Motivation	Types of motivation and how to find and maintain motivation
14	Taking back control	Preparing for challenging situations, social pressure, and impulsive food decisions
15	Reflect and progress	Tools for the next phase of the programme including building self-belief and managing the food environment
16	Accepting thoughts and emotions	Overcoming emotional eating, accepting difficult thoughts, and managing feeling of restriction
17	Moving forwards	Reflecting on the journey so far before moving to the next phase of the programme

During the ‘Growth’ phase, users can still access all features of the app; however, their group will be merged with another group and their health coach may change. The intensity of the programme decreases during ‘Growth’, the message frequency is a minimum of two messages per week, and participation is encouraged less frequently.

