### Intervention components

The intervention components will be delivered as adjuncts to the standard Second Nature programme during the active ‘Core’ phase of the programme only (weeks 1–17).

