### Outcomes and measures

Outcomes and measures are presented in Table 4.

**Table 4 Tab4:** Summary of outcomes and measures

**Outcome**	**Outcome measures**
Primary	• Weight change between baseline and 16 weeks
Secondary	• Weight change between baseline and 24 weeks • Drop-out of programme between baseline and 16 weeks • Drop-out of programme between baseline and 24 weeks • Engagement with the programme between baseline and 16 weeks • Engagement with the programme between baseline and 24 weeks
Exploratory	• Weight change between baseline and 4 weeks • Drop-out of programme between baseline and 4 weeks • Engagement with programme between baseline and 4 weeks

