#### Engagement

Engagement data will be collected to assess whether increased engagement with the programme mediates the association between any observed improvements in weight loss and the four components. Following the procedure used previously [17], engagement will be measured as the cumulative total number of interactions with the three main components of the app: ‘Learn’, ‘Track’, and ‘Support’. ‘Learn’ interactions will be defined as the total of number of articles read. ‘Track’ interactions will be defined as the number of times a participant viewed or had a recorded weight or steps reading. ‘Support’ interactions will be defined as the number of messages sent or received in either the private or group chat. Engagement metrics will be extracted from the app at three time periods, aligning with each follow-up assessment: 0–4 weeks, 0–16 weeks, and 0–24 weeks. The exact cut-off time point for each period will be defined based on the date of the extracted single weight reading.

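### Week-24 outcomes are taken after the randomised groups have been merged, but the engagement count and the week-24 model take no account of this

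*Protocol article*

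**What the plan says.** All references are to the protocol article.

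- **Randomisation:** the unit is the closed group. "Each eligible group will be cluster randomised to one of 16 experimental conditions". For groups not of size 28 to 32: "Groups in which the number of participants falls outside this range will continue to the standard Second Nature programme".
- **Intervention components:** the four components are delivered "during the active ‘Core’ phase of the programme only (weeks 1–17").
- **Core intervention:** 'Growth' covers weeks 18 to 34. The text after Table 3 says that in this phase "their group will be merged with another group and their health coach may change". It does not say how partner groups are chosen or on what date the merge happens.
- **Table 4:** the primary outcome is at 16 weeks. The secondary outcomes include "Weight change between baseline and 24 weeks", and drop-out and engagement over the same period.
- **Weight:** the reading windows are weeks 14–18 for week 16 and weeks 20–28 for week 24. The reading nearest the mid-point is taken.
- **Engagement:** 'Support' is the "number of messages sent or received in either the private or group chat". Each period ends on the date of the extracted weight.
- **Statistical Analysis, primary objective:** one repeated-measures model covers weeks 4, 16 and 24. Participant is the only random effect named.

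The outcome, sample-size and analysis sections do not mention the merge.

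**The concern.** A cluster trial relies on knowing which people share an environment. Up to week 17 that is the randomised group, with one chat and one coach. From 'Growth' onwards it is a larger unit that randomisation did not create. Two consequences follow for the week-24 results.

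First, a participant's count of group-chat messages received then includes traffic from the partner group. That traffic is not an effect of the participant's own components. Engagement is a secondary outcome and also the proposed mediator, so the problem carries into any mediation analysis that uses 0–24 week counts.

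Second, week-24 weights may be correlated within the randomised group and also within the merged group. A model with a participant effect alone allows for neither, so its week-24 intervals would be too narrow if such correlation exists.

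**Working it through.** **1. Order of events.** Components end at week 17, 'Growth' starts at week 18, and week-24 weights are read in weeks 20–28. If the merge comes at the start of 'Growth', which is the natural reading, every week-24 weight follows it. Weeks 18–24 are 7 of 24 follow-up weeks (29%). Weeks 18–28 are 11 of 28 (39%). The week-16 window only touches week 18 at its edge, and the rule favours readings near week 16.

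**2. Engagement.** The 0–24 week count stops at the date of the extracted weight. Time in the merged chat therefore varies between participants from about 20 − 18 = 2 weeks to 28 − 18 = 10 weeks. Joining two groups of similar size roughly doubles the people whose messages can be received. If a group with a component is joined to one without it, both receive nearly the same post-merge group traffic, so that part of the count cannot separate them. If partners are unrelated to condition, the merge adds noise and does not favour either level.

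**3. The plan's own power (week 16).** Inputs from Sample size: 48 groups, 15 analysed per group, cluster-size SD 5, ICC 0.01, alpha 0.10 (taken as two-sided), SD 4 kg.

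- n per component level = 48 × 15 / 2 = 360.
- Design effect = 1 + ((CV² + 1)m − 1) × ICC, with CV = 5/15 and m = 15: 1 + (16.667 − 1) × 0.01 = 1.157.
- Effective n = 360 / 1.157 = 311.
- For d = 0.188: 0.188 × √(311/2) = 2.345, and 2.345 − 1.645 = 0.700, which gives 75.8%.
- For d = 0.25 and 0.22 the same steps give 93.0% and 86.4%.
- A noncentral t with 32 to 46 degrees of freedom gives 92.0–92.3%, 85.1–85.5% and 74.2–74.7%.

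The stated 92%, 85% and 75% reproduce. They refer to week 16 and stand.

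**4. Illustration for week 24.** These assumptions are not in the article: trial groups merge in pairs into 24 units of 30 analysed, the cluster-size SD is 5√2 = 7.07, the ICC is fully shared, and the component level is constant within each merged unit.

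- CV² = (7.07/30)² = 0.0556.
- Design effect = 1 + (1.0556 × 30 − 1) × 0.01 = 1.307.

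| ICC | Power for 0.75 kg, randomised groups | Power for 0.75 kg, merged pairs |
|---|---|---|
| 0.005 | 78.4% | 75.9% |
| 0.01 | 75.8% | 71.3% |
| 0.02 | 71.1% | 63.3% |
| 0.05 | 59.6% | 47.6% |

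At ICC 0.01, intervals that allow for merging are √(1.307/1.157) = 1.06 times as wide as those that allow for the randomised group alone. If the analysis ignores clustering altogether, a nominal 10% test has an effective critical value of 1.645/√1.157 = 1.53 without merging (about 12.6% two-sided). With merging it is 1.645/√1.307 = 1.44 (about 15.0%).

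**5. How likely is cross-condition merging?** The article does not say. Forty-eight groups over 16 conditions is three per condition if balanced. Three is odd, so merging in pairs could not keep every group within its own condition without partners from outside the trial. If the 48 trial groups were paired at random, 2/47 = 4% of partners would share the condition and 24/47 = 51% would have the opposite level of a given component. These two figures depend on that assumed pairing. In practice recruitment is spread over January to August 2024, and non-trial groups may also be partners.

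**The case against.** The strongest reply is that little of the trial is exposed. The primary outcome, its power and the 0.75 kg threshold are all at week 16. The components stop before the merge, so nobody receives another condition's component, and only indirect carry-over through peers or a coach is possible. The week-24 contrast can fairly be read as the effect of the components followed by the provider's usual 'Growth' phase, a sensible question in a routine-service setting. A pairing rule is operational detail that an article may leave to the full protocol. All of this stands.

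It also stands that the power loss in the table is not a general forecast. If merged units contain both levels of a component, their shared variance partly cancels in the contrast, and the loss is smaller.

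The reply does not reach the two analysis points. The engagement definition and the model are stated in the article. Both apply to week-24 data collected after a merge that the article also states.

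**Conclusion.** The point holds for the week-24 secondary outcomes only. They are taken after the randomised groups were merged, possibly with groups on another condition or outside the trial. As written, 0–24 week engagement includes traffic set by the merge partner, and the week-24 model ignores dependence within randomised and merged groups. Weight and drop-out are exposed less directly than engagement. The size is modest at the planned ICC: about 4 to 5 points of power for 0.75 kg under the assumptions in the illustration, and more if the ICC is larger. It rests on the merge coming at or near week 18.

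A reader might infer more, and the documents do not support it:

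- *That conditions are mixed.* Merging within a condition is not excluded, so this remains a possibility.
- *That week-24 data no longer belong to the randomised clusters.* Every participant keeps the randomised group and condition.
- *That blinding fails from week 18.* The article states "All participants will be blind to treatment allocation". Loss of blinding would need both cross-condition pairing and disclosure in the chat, and it would come after the components had ended.
- *That the primary result is compromised because its window runs to week 18.* The nearest-reading rule makes this negligible. Week-24 data do enter the same model, but with component-by-time terms.

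**What to change.** 1. **Record and model the merge.** For each randomised group, record merge date, partner group, partner condition (or non-trial) and coach. Analyse week-24 outcomes by the originally randomised group with a group-level cluster term. Add the merged group as a further random level acting at week 24, at least as a sensitivity analysis, because with about 24 merged units its variance will be poorly estimated. Where the partner is a non-trial group, the extra level coincides with the randomised group and costs nothing.
2. **Engagement.** For the 0–24 week count, leave out group-chat messages received after week 17. Keep the published definition as a sensitivity analysis. Do not rest mediation on unadjusted 0–24 week counts.
3. **Wording.** Report week-24 effects as effects after merging into 'Growth' groups, and state the pairing rule that was used.

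The cost is small. The changes need merge records and message data from the provider's app and a few lines of analysis, and they remain possible after recruitment if those records are held. The drawbacks are a small departure from the previously used engagement definition and slightly wider week-24 intervals if merged groups share a condition (about 6% in the illustration). Restricting which groups may be merged is not asked for: it would change the provider's operations in a trial already under way and is not clearly cheap.

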### Intervention components

The intervention components will be delivered as adjuncts to the standard Second Nature programme during the active ‘Core’ phase of the programme only (weeks 1–17).

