#### Coaching drop-in webchat sessions (Y/N)

Systematic reviews have shown that frequent contact with a dietitian or therapist is associated with improved weight loss [20, 21]. Participants will either be offered or not offered (core programme) a designated 30-min time slot where their health coach will be ‘live’ in the private chat. This provides a platform for participants to receive timely responses to questions, seek guidance, and receive personalised support as well as providing regular, ongoing accountability. At the end of the first week of the programme, participants will be sent a link to schedule a timeslot to ‘drop-in’ with their health coach for personalised support delivered in the private chat function of the app. Health coaches will be able to schedule up to two participants in each 30-min session. At the scheduled time, the health coach will message the participant in the private chat to begin the session. These drop-in sessions will be offered once a week for the first month and then as required thereafter. At the end of each drop-in session, the health coach will send a booking link where the participant can schedule a suitable time for the next drop-in session. The content of the conversation will be largely led by the participant; however, the health coach will be provided with a conversation guide to prompt conversation if necessary.

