#### Goal setting statement (Y/N)

Previous literature has proposed that self-determined motivation, fostered through goal setting, is associated with better weight management [22] and that monitoring goal progress is an effective strategy for promoting goal attainment [23]. Participants will either be asked to complete a goal setting statement alongside regular reflection with their health coach or will not complete a goal setting statement (core programme). Participants will be asked to complete a template in the journal section of the app, where they will be prompted to set an outcome goal (e.g., lose 5 kg by the end of the programme), a process goal (e.g., walk 5000 steps a day), and commit to performing 1–2 actions of their choice (e.g., walk to and from work every day). Participants will then be prompted at the end of each week to answer a series of reflection questions around which actions went well or not so well that week and what they might do differently next week. These reflection questions allow participants to monitor their progress and adjust their strategies accordingly. On a monthly basis, the health coach will prompt the participant to review their goal and ask them whether they wish to adjust the goal. If participants wish to adjust the goal, they will be provided with a new goal setting template to complete in the journal section of the app.

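### The fidelity maximum of 16 goal setting statements does not fit the described schedule, which yields 1 to about 4–5 in weeks 1–17

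*Protocol article*

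**What the plan says.** All references are to the protocol article.

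- **Delivery window (Intervention components).** The four components are added to the standard programme in the core "phase of the programme only (weeks 1–17").
- **Initial goal statement (Goal setting statement).** "Participants will be asked to complete a template in the journal section of the app". The template covers an outcome goal, a process goal and one or two actions.
- **Reflections (same section).** "Participants will then be prompted at the end of each week to answer a series of reflection questions".
- **Goal review (same section).** "On a monthly basis, the health coach will prompt the participant to review their goal". A further template depends on the participant's choice: "If participants wish to adjust the goal, they will be provided with a new goal setting template to complete".
- **Fidelity assessment.** Goal setting has two separate counts per participant: goal setting statements, with a stated maximum of 16, and reflection statements, also with a stated maximum of 16. Drop-in sessions have a stated maximum of 17 and food diaries 17. The section's purpose is to show whether the components were delivered as intended.
- **Drop-in sessions (Coaching drop-in webchat sessions).** The first booking link comes after week 1: "At the end of the first week of the programme, participants will be sent a link to schedule a timeslot". Sessions are then "offered once a week for the first month and then as required thereafter", and "At the end of each drop-in session, the health coach will send a booking link" for the next one.
- **Use of the fidelity data (Statistical Analysis, Process evaluation).** The measures are summarised with descriptive statistics. No threshold is given.

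**The concern.** The maximum for goal statements equals the maximum for the weekly reflections, although only the reflections are described as weekly. Statements are written once and then, at the participant's choice, once a month. A maximum that the described schedule cannot produce is a poor yardstick for whether that schedule was followed.

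Two things are at stake in the process evaluation. First, the goal-statement count will look low beside its printed maximum even when the participant has done all that was asked. The food diary, prompted every week, can reach its maximum of 17. Second, the count is tied to goal changing. A participant who reviews the goal each month and keeps it has complied fully, yet records fewer statements than one who rewrites it each time.

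**Working it through.** **Inputs**

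- Delivery window: 17 weeks (Intervention components).
- Initial statements: 1 (Goal setting statement).
- Review interval: one month (Goal setting statement). The article does not say whether this means 4 weeks or a calendar month (about 4.345 weeks), so both are tried.
- New statements per review: 0 or 1, at the participant's choice (Goal setting statement).
- Stated maxima: 16 goal statements, 16 reflections, 17 drop-in sessions (Fidelity assessment).

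**Step 1. Can the stated 16 be reproduced?** Statements = 1 + number of monthly reviews at which the goal is changed.

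- Reviews every 4 weeks: 17/4 = 4.25, so 4 reviews and at most 1 + 4 = 5 statements.
- Calendar months: 17/4.345 = 3.9, so 3 reviews and at most 1 + 3 = 4 statements.
- Goal kept throughout: 1 + 0 = 1 statement.

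None of these gives 16. A figure of 16 or 17 appears only if a goal statement were written about weekly, and the section gives that frequency to the reflections alone.

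**Step 2. Full adherence set against 16**

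| Fully adherent participant | Statements | Share of 16 |
|---|---|---|
| Keeps the goal at every review | 1 | 6% |
| Changes it at every calendar-month review | 4 | 25% |
| Changes it at every 4-weekly review | 5 | 31% |

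**Step 3. Does the other goal setting count compensate?** Reflections are prompted weekly, so 16 of 16 is attainable. If the two counts were pooled, which the article does not propose, full adherence would give (1 + 16)/32 = 53% to (5 + 16)/32 = 66%. The shortfall thus sits in one of the component's two measures.

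**Step 4. Is the drop-in maximum affected in the same way?** One session a week from week 2 to week 17 gives 16, or 16/17 = 94%. After the first month, however, sessions are held as needed, with no stated cap and a new booking link after each one. A 17th session is possible, so 17 does not contradict the text. It is not a planned number either: a participant who attends only the fixed weekly offers of the first month has 3 or 4 sessions, that is 3/17 = 18% to 4/17 = 24%.

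**The case against.** The fidelity measures are counts. The article defines no percentage score, no adherence threshold and no ranking of components, so a reported median of, say, 1 to 4 statements can be understood whatever maximum is printed beside it. The investigators know their own template is optional. Denominators for descriptive measures are also often left to the full protocol or analysis plan.

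Most of this stands, and it limits the consequence. The percentages above only show scale. It does not remove the inconsistency, because the article does state a maximum, and that figure disagrees with the schedule described a few sections before.

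A reader might infer three stronger things that the documents do not support:

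- **That goal setting as a whole would look undelivered.** It has a second fidelity count, the weekly reflections, which can be complete.
- **That a null goal setting effect would be wrongly put down to non-adherence.** The article assigns fidelity no such role. Under Primary objective, components are selected on the main effect and interaction estimates.
- **That 17 drop-in sessions cannot be reached.** This would need a limit of one session a week after the first month, which the article does not state.

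**Conclusion.** The point holds for one measure. The maximum of 16 goal setting statements contradicts the goal setting section, which yields 1 to about 4–5 statements in weeks 1–17. Read against 16, full adherence shows as 6% to 31%, so the measure understates adherence to the goal-statement part of the component and favours participants who revise their goal over those who keep it.

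This rests on two assumptions: that templates are issued only at the start and at monthly reviews, as described, and that a month means 4 weeks or a calendar month. The documents do not show whether the schedule or the maximum reflects the intention.

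The effect is confined to interpretation of the process evaluation. The primary analysis, power and component selection do not use this count. It is a minor correction, worth making because fidelity is a stated aim of the study.

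**What to change.** Reconcile the goal setting section with the fidelity assessment, stating how many goal statements a participant can be asked for in weeks 1–17. If the monthly, optional schedule is the intended one, replace the maximum of 16 with two measures:

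- initial goal statement completed (yes/no);
- monthly goal reviews answered, out of those prompted, whether the goal was kept or changed.

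The number of revised statements can still be reported as a plain count. The reflection measure can stay as it is.

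For drop-ins no correction is needed. Reporting sessions attended out of those offered or booked would be more informative than a fixed 17, but this is optional.

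The cost is the rewording of one descriptive measure and its extraction from the app records, including replies to review prompts. Nothing changes for participants, and it can be done before the fidelity data are analysed.
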